### Study objectives

Primary objective: To determine the specificity and sensitivity of currently available ambulatory vital signs monitoring equipment for the detection of hypoxia.

Secondary objective: To determine the effect of movement on data acquisition by currently available ambulatory vital signs monitoring equipment.

These objectives will be assessed by comparing continuous peripheral oxygen saturations, pulse rate, heart rate and respiratory rate data from each AM with arterial blood oxygen saturation measured through arterial blood sampling, pulse rate derived from the arterial blood signal, heart rate derived from standard care 3-lead ECG, and respiratory rate derived from capnography and manual counting.

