**Figure 2 F2:**
[figure not shown]
Hypoxia study day set-up. Legend: 1: tablets linked with AMD devices (4 Samsung TAB A, each linked with one AMD: AP-20, WristOX2 3150 BLE, CheckMe^™^ O2 and VitalPatch^®^. 1 iPad four connected to the wavelet). 2: resuscitation trolley and oxygen. 3%–7% oxygen in nitrogen cylinder. 4: hypoxicator apparatus. 5: Philips monitor (model MX450) connected to laptop (IX trend software). 6: drip stand with the arterial line pressure bag.

During the hypoxia exposure phase, oxygen saturations from the ‘clinical standard’ Philips monitor will guide the titration of the hypoxicator. Seven per cent oxygen in nitrogen will be used to further lower FiO_2_ if required. An ABG will be sampled when the participant reaches and remains stable at each pre-specified target peripheral oxygen saturation level (95%, 90%, 87%, 85%, 83%, 80%). We specified these saturations to allow assessment for our use case of prompt detection of hypoxia in normal adult patients in a ward environment, including multiple assessments within the 83%–95% range, and one assessment at the top end of the 70%–80% range, considered severe hypoxia.

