## Analysis

For continuous data we will sample by two methods: (1) simultaneous single data points, (corresponding to the time of ABG sampling where relevant) and; (2) by selecting sampling windows of 5–30 s and comparing data for each device. Data points will be recorded across device time-stamps to ensure accuracy of comparisons.

In accordance with the international standard of pulse oximeter equipment validation (ISO 80601-2-61:2019), the accuracy of the SpO2 measurement will be stated in terms of the root-mean-square (rms) difference between measured values (devices under test) (SpO2i) and reference values (gold standard arterial line and clinical standard) (SRi), as given by:

$$A_{rms}=\sqrt{\frac{\sum_{i=1}^{n}{\left({SpO}_{2i}-S_{Ri}\right)}^{2}}{n}}$$

We will also compute the bias between gold standard, clinical standard and each device under test:

$$B=\frac{\sum_{i=1}^{n}\left({SpO}_{2i}-S_{Ri}\right)}{n}$$

and the precision:

$$s_{res}=\sqrt{\frac{\sum_{i=1}^{n}{\left({SpO}_{2i}-{SpO}_{2fit,i}\right)}^{2}}{\left(n-2\right)}}$$

where SpO2fit is the value of the fitted curve corresponding to the ‘i’th reference value. Simple statistics about the difference among measurements (mean, SD, percentiles, Bland-Altman plots) will be provided for the all the devices under analysis. Identical statistical methods will be applied to assess the agreement between the estimation of the (i) pulse rate from the pulse oximeters, and of the (ii) heart rate and (iii) respiratory rate from the patch, and the corresponding reference measurements.

The performance of each pulse oximeter in detecting hypoxaemia (at each level ≤90%) will be assessed by reporting the optimal sensitivity and specificity pair, identified via Receiver-Operating Characteristic curves.^7 12^

Descriptive statistics will be also computed per participant, per skin type and with and without movement artefacts.

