### Outcome analysis

We will analyse the outcomes on all the participants from whom we collected the data. The accuracy will be compared with the respective reference pulse oximeter. Where paired readings exist (device with clinical or gold standard), they will be included in the analysis. Device readings with no paired clinical or gold standard will be excluded from the analysis.

Primary outcome measure: Sensitivity and specificity for detecting hypoxia at each level ≤90%): The analysis plan detailed above will provide data on correlation of each device with ‘gold standard’ arterial measurements, and their accuracy for the detection of hypoxaemia: The output of this analysis will allow selection of the devices which correlate most closely to the ‘gold standard’ measurements, and provide the highest performance in the detection of hypoxaemia.

Secondary outcome measure: Correlation of device outputs, that is, HR, RR, PR and SpO2, with ECG derived HR, capnography derived RR, arterial blood pulse rate and pulse oximetry, respectively, during movement:

The analysis plan detailed above will provide data on correlation of each device with ‘gold standard’ arterial measurements during protocolised movement tests. The output of this analysis will allow selection of the devices which correlate most closely to the ‘gold standard’ measurements.

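### The primary sensitivity/specificity pair is taken at a ROC-chosen cut-off, so it does not register constant over-reading and does not give accuracy at the displayed SpO2

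*Protocol article*

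**What the plan says.** The primary objective (Study objectives) is "To determine the specificity and sensitivity of currently available ambulatory vital signs monitoring equipment for the detection of hypoxia". Under Outcome analysis the primary measure is "Sensitivity and specificity for detecting hypoxia at each level" at or below 90%; the targets listed for the hypoxia phase make these levels 90, 87, 85, 83 and 80%. The Analysis section fixes how this is summarised: performance "will be assessed by reporting the optimal sensitivity and specificity pair, identified via Receiver-Operating Characteristic curves". It sets no device cut-off, does not define optimal, and does not list performance at the displayed value as an output.

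Outcome analysis then gives the purpose. The results are to pick out the devices that correlate most closely with the arterial reference and "provide the highest performance in the detection of hypoxaemia". The hypoxia-phase section describes the setting as "our use case of prompt detection of hypoxia in normal adult patients in a ward environment".

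The Analysis section also plans agreement measures: "We will also compute the bias between gold standard, clinical standard and each device under test", together with Arms, precision, percentiles and Bland-Altman plots. These are reported beside the primary outcome and are not named as selection criteria.

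**The concern.** Choosing the cut-off by ROC curve, separately for each device and level, lets the cut-off move to absorb any constant calibration error. A device reading 3 points high receives a cut-off about 3 points higher and scores the same as an unbiased one. On a ward, the reading on the display is what gets compared with a saturation level. Over-reading is the error that makes true hypoxia look acceptable, and the primary figures do not register it.

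Two things are at stake. The headline sensitivity and specificity may not describe the equipment as it displays its readings, which is what the objective asks about. And the two selection criteria that the article names share the same blind spot.

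**Working it through.** **Figures in the plan.** The article gives no target or expected sensitivity or specificity, so none can be reproduced. Its only sample-size figure is about 30 full data sets for at least 200 points. With normoxia plus six targets, 200/7 = 28.6, so 29 participants, and 30 × 7 = 210 points. This is consistent, and the point does not depend on it.

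**Step 1: algebra, no assumed figures.** For level L and device cut-off c:

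- Se(c, L) = P(SpO2 ≤ c given SaO2 ≤ L)
- Sp(c, L) = P(SpO2 > c given SaO2 > L)

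Let a second device read b points higher throughout. Then Se₂(c + b, L) = Se(c, L), and likewise for Sp. Over all c, both devices trace the same ROC curve and have the same optimal pair, apart from display rounding and the ceiling at 100%. Correlation is also unchanged by adding b. At the nominal cut-off, however, Se₂(L, L) = Se(L − b, L). With b = 3 and L = 90, the second device performs like an unbiased one judged at 87.

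**Step 2: size.** The documents give no device bias or error SD, so these are assumptions: 30 participants with 7 points each, between- and within-person error SD 1.5 each, SaO2 scatter about target SD 2, integer display, and optimal taken as the largest sum of sensitivity and specificity. Averages over 1,500 simulated studies:

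| Level, bias | Displayed cut-off, Se/Sp (%) | ROC-optimal, Se/Sp (%) |
|---|---|---|
| 90, 0 | 95.3 / 90.0 | 93.4 / 93.6 |
| 90, +3 | 78.4 / 98.8 | 93.2 / 93.6 |
| 90, −3 | 99.7 / 68.3 | 93.3 / 93.6 |
| 80, +3 | 33.7 / 99.4 | 96.4 / 87.1 |

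In sensitivity plus specificity, the gap at level 90 is 187.0 − 185.3 = 1.7 points with no bias and 186.8 − 177.2 = 9.6 points at +3. At level 80 with +3 it is 183.5 − 133.1 = 50.4 points.

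**Step 3: sensitivity to the assumptions.** A separate simulation used SaO2 scatter 1.5.

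- Level 90, bias −3, 0, +3: the best cut-off moves 86, 89, 92, and the optimal pair stays near 91%/94–95%.
- Level 85, bias +3: 56.0%/98.7% displayed against 88.8%/89.0% optimal. With zero bias the displayed pair is 89.1%/89.3%.
- Level 90, bias +3, total error SD 1, 2, 3: displayed sensitivity 80%, 78%, 76%; optimal 95%, 92%, 88%.
- Level 80, total error SD 2: with zero bias, 78.1%/94.3% displayed against 95.4%/85.2% optimal; with +3, 26.9%/99.5% against 95.5%/85.2%. Part of the sensitivity gap at 80% is therefore a trade-off along the curve that exists without bias. The fall in displayed sensitivity from 78.1% to 26.9% is due to the bias.

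**Step 4: the other measures.** In that second simulation (total error SD √(1.5² + 1.5²) = 2.12), moving from bias 0 to +3 leaves correlation almost unchanged (0.946 to 0.943), while Arms rises from 2.1 to 3.4. Arms and B show the offset; the named selection criteria do not.

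**Step 5: same-data choice of cut-off.** Apparent minus true sensitivity plus specificity was 2.1–2.3 points at level 90 and 4.7–5.0 at level 80.

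**The case against.** A reader might infer that the plan hides device bias altogether. It does not. The Analysis section reports B for every device, along with Arms and Bland-Altman plots, and a device 3 points high would show B near +3. The limitation applies to the primary pair and the named selection criteria.

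A reader might also infer that a poorly calibrated device will be selected. The article does not say that selection ignores the agreement measures. Outcome analysis refers back to the whole analysis plan, and correlation may be meant loosely as agreement. What stands is that the only criteria actually named, taken literally, are insensitive to a constant offset.

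ROC analysis is a legitimate description of what a device can discriminate, and useful in a phased project that goes on to test devices in hospital patients. Nothing here argues for removing it. If device-specific thresholds were the aim, however, the cut-offs would have to be reported with the pairs, and the stated output is the pair alone.

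It is also tempting to call the primary figures materially inflated because the cut-off is judged on the data that chose it. The article says "We will analyse the outcomes on all the participants from whom we collected the data" and mentions no validation step, but that is silence. A fuller analysis plan may contain one, and the optimism is only a few points.

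Finally, the magnitudes rest on an assumed constant bias, assumed error SDs and an assumed meaning of optimal. This is fair, and it limits the size of the effect but not the algebra in Step 1.

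**Conclusion.** The concern holds for the primary pair and the named selection criteria, and no further. The plan fixes a primary summary that is unchanged by a constant device offset, names a second selection criterion with the same property, and does not state accuracy at the displayed SpO2, which the ward use case needs. The separately planned bias, Arms and Bland-Altman results keep the offset visible but do not correct the primary sensitivity and specificity.

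The size depends on the true device bias. For positive bias the direction is clear: displayed sensitivity falls while the ROC pair stays put. At an assumed +3 points, the optimal pair shows about 15 points more sensitivity at level 90% (93.2 − 78.4 = 14.8) and about 63 more at level 80% (96.4 − 33.7 = 62.7), with lower specificity in both cases. With unbiased devices the matter is minor at 90%. Same-sample optimism is a side point.

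This should be fixed. It does not threaten the design or the data collection.

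**What to change.** 1. Make the primary result sensitivity and specificity at the nominal cut-off: device SpO2 ≤ L against ABG SaO2 ≤ L, for each level L of 90, 87, 85, 83 and 80%.
2. State that device selection uses these figures together with bias B and Arms. If correlation was meant as agreement, say so.
3. Keep the ROC curve and optimal pair alongside as a measure of discrimination, define optimal, and always show the chosen cut-off.
4. Optionally, give a participant-level cross-validated or bootstrap figure with the optimal pair.

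The paired device and ABG readings are already planned, so no new data are needed. The cost is a few lines of wording and code, and less favourable headline figures for biased devices.

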### Outcome analysis

We will analyse the outcomes on all the participants from whom we collected the data. The accuracy will be compared with the respective reference pulse oximeter. Where paired readings exist (device with clinical or gold standard), they will be included in the analysis. Device readings with no paired clinical or gold standard will be excluded from the analysis.

Primary outcome measure: Sensitivity and specificity for detecting hypoxia at each level ≤90%): The analysis plan detailed above will provide data on correlation of each device with ‘gold standard’ arterial measurements, and their accuracy for the detection of hypoxaemia: The output of this analysis will allow selection of the devices which correlate most closely to the ‘gold standard’ measurements, and provide the highest performance in the detection of hypoxaemia.

Secondary outcome measure: Correlation of device outputs, that is, HR, RR, PR and SpO2, with ECG derived HR, capnography derived RR, arterial blood pulse rate and pulse oximetry, respectively, during movement:

The analysis plan detailed above will provide data on correlation of each device with ‘gold standard’ arterial measurements during protocolised movement tests. The output of this analysis will allow selection of the devices which correlate most closely to the ‘gold standard’ measurements.

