## Introduction

Failure to recognise and act on physiological indicators of worsening acute illness in hospital wards is a prevalent problem recognised over twenty years ago.^1^ Current practice involves the use of early warning scoring systems which monitor standard vital signs. These include intermittent measurements of pulse rate, respiratory rate, blood pressure, oxygen saturations and temperature. The frequency of vital signs measurements is usually guided by the clinical condition of the patient.

Intermittent measurement of these vital signs can be time consuming for healthcare professionals,^2^ and therefore the desired frequency of observations is often not achieved.^3^ Infrequent measurement of vital signs may also miss clinical deteriorations between these measurements.^4^ Thus, more sustainable, accurate and less time-consuming monitoring methods would be highly desirable.

Wearable ambulatory monitors (AM) may provide an alternative to intermittent vital signs monitoring by enabling the continuous monitoring of vital signs parameters. In addition to reducing the burden of intermittent measurement of vital signs on staff, continuous monitoring has the potential to facilitate earlier detection of deranged physiological parameters.^5^ A major barrier to the clinical implementation of these wearable devices is their uncertain reliability, efficiency and data fidelity.^6^ In particular, the effect of motion on its accuracy is underinvestigated. Recent work by Louie *et al*
7 tested four non-ambulatory pulse oximeters and found that motion impaired performance throughout a clinically relevant range of measurements. Less accuracy was reported at lower arterial oxygen saturations (SaO_2_) which is undesirable in clinical practice.^7^

This study is part of the Virtual High Dependency Unit (vHDU) project, a collaboration between the Institute of Biomedical Engineering and clinicians from the Nuffield Department of Clinical Neurosciences at the University of Oxford. This is a phased project aiming to refine and integrate ambulatory monitoring systems for use in clinical practice. Previous phases have tested device wearability and in situ testing on hospital wards. The purpose of this study is to test the performance of selected devices in a simulated clinical setting which will involve participant movement and inducing low peripheral oxygen saturations.

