### Data quality and completeness

Manually entered data (eg, ABG data, RR count, etc) will be subject to a 10% data validation check.

To ensure correct time-stamping, all ABG collection times will be recorded both using the vHDU app and manually recorded time (hh:mm:ss). Each participant AMD, gold and clinical standard, and time-stamp data will be plotted and audited visually up to 1 week after participation to assess data completeness. Each participant dataset will be deemed complete if there are test device data to answer either the primary or secondary objective, including both gold standard and clinical standard reference data.

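### Only paired readings are analysed, so reference points where a device is blank drop out unreported, and no outcome measures the data acquisition that the secondary objective names

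*Protocol article*

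**What the plan says.** All places are in the protocol article.

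- **Outcome analysis, inclusion:** "Where paired readings exist (device with clinical or gold standard), they will be included in the analysis".
- **Outcome analysis, exclusion:** "Device readings with no paired clinical or gold standard will be excluded from the analysis". This covers a device value without a reference. Nothing is said about a reference value without a device value.
- **Primary outcome:** "Sensitivity and specificity for detecting hypoxia at each level ≤90"%. The Analysis section obtains it by "reporting the optimal sensitivity and specificity pair, identified via Receiver-Operating Characteristic curves".
- **Secondary objective (Study objectives):** "To determine the effect of movement on data acquisition by currently available ambulatory vital signs monitoring equipment".
- **Secondary outcome (Outcome analysis):** "Correlation of device outputs, that is, HR, RR, PR and SpO2, with ECG derived HR, capnography derived RR, arterial blood pulse rate and pulse oximetry", during movement.
- **Data quality and completeness:** each participant's data are "plotted and audited visually up to 1 week after participation to assess data completeness". A data set counts as complete if it has device data for either objective, together with both references.
- **Introduction:** the barrier to clinical use of these devices is "their uncertain reliability, efficiency and data fidelity".

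The Outcome analysis section adds that the results will be used to select devices.

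**The concern.** A wearable oximeter can fail in two ways: it can show a wrong value, or it can show none. The planned statistics (Arms, bias, precision, Bland-Altman plots, ROC curves) see only the first kind of failure. For the use the protocol describes, prompt recognition of hypoxia on a ward, a blank display at a hypoxaemic moment is also a failure to detect.

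Under a pairs-only rule, a device that suppresses its output when the signal is poor can look better than one that keeps reporting. Because the results feed device selection, this could change which device is preferred.

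The secondary objective has a related gap. It asks what movement does to data acquisition, but the outcome attached to it is calculated only where acquisition succeeded.

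**Working it through.** **1. The plan's own figure.** The Sample size section asks for at least 200 data points and gives about 30 full data sets. The arithmetic is not shown.

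- Seven points per participant (normoxia plus the six target levels): 200/7 = 28.6, so 29 participants, and 30 × 7 = 210. This agrees with 30.
- Six points per participant: 200/6 = 33.3, so 34 participants, and 30 × 6 = 180. This does not agree.

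The seven-point basis is therefore an inference. On that basis, a blank rate above 1 − 200/210 = 4.8% takes a device below 200 pairs; at 10%, 189 remain.

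**2. Hypoxaemic reference points.** Five of the six target levels are at or below 90% (90, 87, 85, 83, 80). That gives 30 × 5 = 150 points per device. The count is nominal, because titration follows the bedside oximeter and the arterial values may differ.

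**3. Effect of blanks on sensitivity.** Let N be the hypoxaemic reference points, m the share of them with no device value, and TP the paired points correctly flagged at the chosen threshold.

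- Pairs only: Se_paired = TP / [N(1 − m)]
- All points, blank = not detected: Se_all = TP / N = Se_paired × (1 − m)
- Overstatement factor: Se_paired / Se_all = 1/(1 − m)

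The document gives neither m nor Se_paired, so both are assumed below.

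| Assumed m | Se_all if Se_paired = 80% | 90% | 100% |
|---|---|---|---|
| 5% | 76% | 85.5% | 95% |
| 10% | 72% | 81% | 90% |
| 20% | 64% | 72% | 80% |
| 30% | 56% | 63% | 70% |

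Worked count at 90% and m = 10%: 15 of 150 points are blank and 135 are paired, with 0.90 × 135 = 121.5 detected. Then 121.5/135 = 90%, but 121.5/150 = 81%.

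At a single level (30 points), a device blank at 6 and right at 24 is reported as 24/24 = 100%, although it detected 24/30 = 80%.

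**4. Effect on ranking (assumed figures).** Device A has paired sensitivity 95% and 20% blanks: 0.95 × 0.80 = 76%. Device B has 88% and 2% blanks: 0.88 × 0.98 = 86.2%. Pairs-only sensitivity favours A; detection over all points favours B.

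**5. Dependence on the scoring rule.** If a blank were treated as an alert, the case in step 3 gives (121.5 + 15)/150 = 91%. Sensitivity would then not be overstated, and the cost would fall on specificity.

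**6. Secondary objective against secondary outcome.** No arithmetic is needed.

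| Element | What it addresses |
|---|---|
| Secondary objective | Effect of movement on data acquisition |
| Secondary outcome | Correlation of acquired values with references |
| Completeness audit | Visual quality control per participant; not an outcome |
| Descriptive statistics by movement artefact | Values obtained |

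None of these is a measure of data loss or availability.

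**The case against.** **The text does not say that blanks are discarded.** This is correct. The quoted sentence is an inclusion rule, and the explicit exclusion is the reverse case. A reader might infer a stated rule to delete blanks, but there is none. The loss follows from combining the inclusion rule with formulas that all need a device value, and nothing in the article brings those points back.

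**Scoring of absent values belongs in the analysis plan.** In general it does. Here, however, the article itself fixes both the analysis set and the secondary outcome.

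**Movement does not drive sensitivity.** A reader might infer that dropout during movement inflates the primary result. The document does not support that. Movement is a separate seated stage before hypoxic gas is given. Hypoxia samples are drawn semi-recumbent at a stable level, with staff assigned to troubleshoot devices and watch data quality, and the 5–30 s windows may bridge short gaps. Blanks at hypoxaemic points may be few. Movement blanks bear on the secondary objective.

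**The objective is defined by its assessment sentence.** Study objectives says both objectives will be assessed by comparing device data with the references, so agreement during movement could be all that was meant. That makes the mismatch partly one of wording. But a comparison of values obtained still does not measure how often values were obtained.

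**Counting every blank as not detected creates a new bias.** This stands if the rule is applied to all blood gas points. Blanks at non-hypoxaemic points would become true negatives, and a device that was always blank would score 100% specificity. The fix below avoids this.

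**Conclusion.** The point holds in two parts.

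The first is conditional. If devices are blank at hypoxaemic reference points, and a blank is regarded as a missed detection, pairs-only sensitivity is overstated by 1/(1 − m). At an assumed paired sensitivity of 90%, that is 4.5 percentage points at m = 5% and 9 points at m = 10%. The actual size cannot be known from the document. The higher rates in the table only show the range and have no support for resting, supervised volunteers. It would be too strong to say that the primary analysis is shown to be biased, or that dropout has been shown to be non-random. The Introduction reports only that, in a study of non-ambulatory oximeters, motion impaired performance and accuracy fell at lower saturations.

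The second rests on no assumed figure. The secondary objective names data acquisition, and no outcome measures it.

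Both parts bear on the device selection that the protocol states as its purpose, and both can be corrected cheaply.

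**What to change.** 1. Make data availability a secondary outcome: the share of time, and of reference points, with a valid value. Report it per device at rest in normoxia, for each movement and at each saturation level. Where the records allow, separate device blanks from losses in the study's own tablet link.
2. Keep the pairs-only ROC, Arms and bias results. Beside them, report sensitivity at the ROC-selected threshold, with all reference points at SaO2 ≤90% while the device was worn as denominator and blanks counted as not detected. State the rule and the matching window in advance.
3. Do not credit blanks at non-hypoxaemic points as true negatives. Report specificity on pairs, with the blank rate next to it.
4. Use availability together with accuracy when selecting devices.

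**Cost:** changes of wording and slightly more analysis. Device data are recorded continuously and activities are time-stamped, so no new measurements should be needed. Sensitivity figures may look less favourable.
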